#### Monthly assessments

##### Juveniles

The monthly questionnaire for juveniles contains 34 items. It measures: (1) Externalizing behavior using five items of the Externalizing Scale of the YSR [43], of which some items are composites of multiple original items, by for example asking whether the juvenile stole something instead of differentiating between stealing inside and outside of the home; (2) Delinquency using six items of the SDB [45], of which some items are composites; (3) Substance use using six items, inquiring for both alcohol and drugs if the juvenile used the substance in the past week, on how many days, and whether the usage was representative for the past month; (4) Contact with deviant peers using two items of the BPQ [47], and one item asking whether the juvenile hang out with friends that fight; (5) Parenting using one item of the NPQ [53], one item of the IPPA [50, 51], two items of the NRI [49], and six items asking about monitoring, harsh punishments, and whether the juvenile got along with their caregiver; (6) Cognitive distortions using three items of the Aggression and Justification Scale of the BITI [57]; and (7) Treatment characteristics using one item of the Relationship with Interventionist Scale [60].

Items are measured using a 6-point Likert scale. Answer options are 1 = *never* to 6 = *often* for YSR and BPQ items, 1 = *0 times* to 6 = *more than 10 times* for SDB items, 1 = *little to none* to 6 = *the most* for NRI items, 1 = *almost never* to 6 = *almost always* for the IPPA item, and 1 = *totally disagree* to 6 = *totally agree* for other items.

##### Caregivers

 The monthly questionnaire for caregivers contains 16 items. It measures: (1) Externalizing behavior using three items of the CBCL [44], of which some are composites; (2) Parenting using three items of the NPSI [52], two items of the NRI [49], one item of the NPQ [53], and four items asking about monitoring, harsh punishment, and whether the caregiver got along with their child; and (3) Treatment characteristics using one item of the Relationship with Interventionist [60] and two items measuring direct treatment time (for more information, see the description in the section Treatment Characteristics).

Items are measured using a 6-point Likert scale. Answer options are 1 = *never* to 6 = *often* for CBCL items, 1 = *little to none* to 6 = *the most* for NRI items, and 1 = *totally disagree* to 6 = *totally agree* for other items.

### Data management

Contact data is stored in a digital double encrypted database. Research data is stored and will be analyzed in separate files, without direct links to the participants. Participants can fill out questionnaires on paper or online using personalized links send through Qualtrics, the online survey tool of Utrecht University. All completed paper documents are stored secured at Utrecht University, and will be scanned and directly stored on YODA, a research data management service that is compliant to the guidelines of General Data Protocol Regulation. Completed paper questionnaires will additionally be entered into Qualtrics by a researcher. Information from therapist files and judicial records will be coded into SPSS or JASP files. All data will be stored directly on YODA. Only the researchers involved in this study have access to the data.

### Plan of data analysis

Data will be analyzed according to the intention-to-treat principle and will also be analyzed separately for the completers only. Little’s test will be used to test whether data is missing at random. If so, missing data will be imputed so that all participants can be included in the analyses. Possible baseline differences in demographic characteristics between the participating and non-participating FAST-clients will be checked by means of chi-square analyses and independent t-tests to investigate the representativity of the included sample. In addition, possible baseline differences in demographic characteristics and outcome variables between the FASTb and FASTr condition will be checked by means of (M)ANOVA (continuous variables) and chi-square analyses (categorical variables). If (some of) these variables show significant differences between FASTb and FASTr conditions, they will be entered as covariates in all (regression) models testing the effectiveness of the intervention.

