### Blended care: FAST blended (FASTb)

Prompted by the worldwide Covid-19 pandemic, a blended version of FAST has been developed (FASTb). Content wise, FASTb is nearly identical to regular FAST (FASTr). However, FASTb offers a combination of face-to-face and online treatment, consisting of a minimum average of 50% online direct treatment time over the duration of the intervention (such as phone calls, video calls, text messages, and eHealth; for more information, see Conditions). Blended interventions have several benefits over sole face-to-face intervention [12]. They increase accessibility and allow clients to work on therapy at any given moment, allow for precise registration of treatment delivery, increase (online) access to training materials for clients, involve lower time commitment for clinicians, and involve lower costs [13]. Moreover, blended interventions might be especially beneficial in the treatment of juveniles with antisocial behavior, as these interventions are expected to be even more flexible in adhering to the RNR principles than sole face-to-face treatment [14]. Blended intervention is less dependent on time and place, which increases the flexibility and accessibility of the intervention. It fits the increased use of the internet by juveniles and can be more responsive to the individual learning style or preference by offering both reading and visual material. Thereby, blended intervention might help reaching more clients and increase the involvement of this hard-to-reach target group in treatment. In fact, the integration of technological platforms in interventions has been employed to better reach juveniles and their families [15].

Despite these possible benefits, therapist implementation of blended interventions in forensic mental health care has been found to be disappointing, even though therapists viewed blended interventions as having potential to improve treatment quality [16]. The study of Kip et al. [17] investigated what could increase therapist use of blended interventions in forensic mental health care. Therapists indicated a need for more technological knowledge and highlighted the importance of the basic technological prerequisites, such as a stable internet connection. Further, they voiced that more research should be conducted to determine the actual effectiveness of blended interventions in the forensic field, and to specifically focus on why and for whom blended interventions work.

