#### Sample size calculation

Based on a MANOVA a priori power analysis, a group of *n* = 120 (*n* = 60 per group) will allow us to identify – with a power of 0.80, an alpha of 0.05 – small differences (d = 0.15) in effectiveness between FASTb and FASTr (G*power 3.1) [40]. To account for possible drop-out, which was approximately 20% in our previous comparable study [41], *n* = 200 participants will be recruited. Based on the number of juveniles referred to FAST at the treatment sites participating in this project (approximately 120 juveniles yearly), and participation rates of 70–90% in our earlier comparable studies [41, 42], it is considered feasible to include in total *n* = 200 juveniles and their caregivers within three years.

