##### Treatment characteristics

The following treatment characteristics will be assessed: treatment integrity, including adherence to the assigned level of online therapy, treatment duration, intensity and completion, therapist-client alliance, motivation, expectancies, and cooperation.

Treatment integrity will be measured at T2 using the FAST evaluation form, which is filled out separately by juveniles, caregivers, and therapists as part of the standard FAST procedure. The FAST evaluation form assesses whether the working elements of FAST were sufficiently applied during treatment (i.e., juveniles and caregivers report whether treatment goals were set in collaboration with them and therapists report whether they made sufficient use of cognitive behavioral therapy techniques) and whether treatment duration and appointment frequency matched the recidivism risk level. Treatment integrity will be scored in percentages, where a higher percentage indicates higher treatment integrity.

Adherence to the assigned level of online therapy within FASTb and FASTr will be measured at T2 by calculating the average percentage of online and face-to-face direct treatment time over the duration of intervention in two ways. First, it will be calculated based on registered direct time by therapists in their appointment agendas. Registration codes indicate whether the direct treatment time was online or face-to-face. In addition, caregivers will be asked monthly to report how many online appointments and how many face-to-face appointments they have had with their therapist in the past month. At T2, the average percentage of online and face-to-face appointments over the duration of the intervention will be calculated based on both measures.

Treatment duration, intensity, and completion will be assessed using case file analysis. Duration and intensity will be calculated based on the registered direct treatment time by therapists in their appointment agendas. Treatment duration will be measured in weeks and treatment intensity will be measured in average hours of direct treatment time per week. Treatment completion will be assessed by coding whether FAST completion was registered as positive or negative.

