In the recruitment and data-collection of this study, several challenges are expected. One will be the recruitment and retainment of *n* = 200 FAST clients, as the target group is generally hard to reach and motivate for research. We have planned several actions to promote participation and retainment. First, we include six treatment sites to be able to approach sufficient clients. If influx of FAST clients or willingness of FAST clients to participate in the study are lower than expected, other treatment sites can participate as well. To ensure an efficient participation of a new treatment site, all treatment sites of de Waag that offer FAST have been informed of the study, and the responsible FAST therapists of all treatment sites have been informed about the study procedure. Second, we will invest time and effort in the recruitment and retention of participants. The research team will adjust the recruitment and data collection to the preferences of the participants for timing and location. For instance, questionnaires can be filled out on paper or online, or can be taken in interview form by trained research assistants during (video) calls or home visits. Third, participants will receive a financial compensation for each completed measurement. When completing all measurements, each participant will receive around 50 euros. We have good experiences in increasing motivation to participate by paying participants for their participation [41, 42]. Fourth, twice a year, we will organize meetings with our advisory council, which consists of professionals and former FAST-clients, to keep reflecting on our study procedure and gain new ideas on how to promote study participation and retention.

A second challenge of the study can be therapist adherence to the set percentages of direct online treatment time for FASTb and FASTr. Percentages of direct online treatment time are not calculated automatically within the appointment registration system. Therefore, percentages will be calculated every three months. In addition, the researcher and therapists are in close contact and meet frequently to discuss potential issues regarding adherence.

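### Missed online shares pull the intention-to-treat contrast towards the hypothesised equality, and neither the completers-only analysis nor the adherence moderator corrects for this

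*Protocol article*

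**What the plan says.** The Aims of the study section expects the two versions to be equally effective on the primary and secondary goals. The Conclusion looks to a finding that blended treatment is at least as effective. The condition descriptions set the online share of direct treatment time at no more than 10% in FASTr and at an average of at least 50% in FASTb.

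The protocol sees the risk of missed shares. In the Discussion: "A second challenge of the study can be therapist adherence to the set percentages of direct online treatment time for FASTb and FASTr". In the Background, about earlier work in this field: "therapist implementation of blended interventions in forensic mental health care has been found to be disappointing". It plans to calculate the percentages every three months and to discuss adherence with therapists. It also measures the result: "Adherence to the assigned level of online therapy within FASTb and FASTr will be measured at T2", from therapists' agenda registrations and from monthly caregiver counts of appointments.

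On analysis, the Plan of data analysis says: "Data will be analyzed according to the intention-to-treat principle and will also be analyzed separately for the completers only". The Effectiveness subsection compares the assigned conditions by analysis of covariance with the T1 score as covariate, chi-square tests and survival analyses. The only completion variable described, under Treatment characteristics, is whether FAST completion was registered as positive or negative. Adherence to the online level is listed among the treatment characteristics. The Moderation subsection handles these with a moderator-by-condition interaction, followed by analyses of covariance in the split file.

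**The concern.** In a superiority trial, imperfect delivery makes intention-to-treat conservative. Here it works the other way. If FASTb families receive less online treatment than planned, or FASTr families more, the arms converge and any true deficit (or benefit) of FASTb is understated. A small, non-significant difference is the result the trial hopes for. It could mean that the two formats work equally well, or that the trial did not separate them enough to tell.

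The two analyses that might distinguish these readings do not. A family that finishes FASTb with a low online share can still count as a completer. Splitting or interacting on achieved adherence compares groups formed after randomisation, which may differ in severity, motivation or therapist. At stake is the main claim about blended care.

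**Working it through.** **The plan's own figures.** The protocol gives no expected adherence rate and no power under imperfect adherence, so there is no figure to reproduce on this point. Its sample-size statement concerns "small differences (d = 0.15) in effectiveness between FASTb and FASTr" with 60 per group. Read as Cohen's d, two-sided, that needs 2 × (1.96 + 0.84)² / 0.15², about 698 per arm. That mismatch is a separate matter and nothing below depends on it.

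**Inputs from the protocol**
- 200 recruited, 1:1, about 20% drop-out: 200 × 0.80 = 160, or 80 per arm.
- Separation implied by the two limits: 50 − 10 = 40 percentage points. The limits are a minimum and a maximum, so 40 is a benchmark and not a target.
- Alpha 0.05, taken as two-sided because the sidedness is not stated.

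**Assumptions (not in the protocol)**
- T1-outcome correlation r = 0.6.
- A true FASTb deficit of 0.40 SD at full separation.
- Effect proportional to f, the fraction of the intended separation achieved.

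**Step 1: what f might be.** Average shares of 40% against 15% give 25/40 = 62.5%. Shares of 35% against 15% give 20/40 = 50%.

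**Step 2: precision.** SE = √(1 − r²) × √(2/n) = √0.64 × √(2/80) = 0.8 × 0.1581 = 0.1265 SD.

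**Step 3: power.** Power = Φ(0.40f/SE − 1.96) + Φ(−0.40f/SE − 1.96).

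| f | Diluted difference (SD) | Power |
|---|---|---|
| 1.0 | 0.40 | 0.885 |
| 0.7 | 0.28 | 0.600 |
| 0.5 | 0.20 | 0.353 |
| 0.3 | 0.12 | 0.158 |

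At half separation, about 65% of such trials (1 − 0.353) would show no significant difference. With r = 0.4 or 0.7, power at f = 0.5 is 0.28 or 0.43.

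**Step 4: the interval.** The half-width is 1.96 × 0.1265 = 0.248 SD. Expressed per full separation at f = 0.5, it is 0.248 / 0.5 = 0.496 SD. As evidence about the formats as defined, the intention-to-treat interval then looks twice as precise as it is.

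**Step 5: a second dilution model.** Suppose each family either receives its assigned format or receives the other one. The retained fraction is 1 − (proportion missed in FASTb) − (proportion missed in FASTr). For a true d of 0.50, 80 per arm and no covariate, SE = 0.1581.

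| Missed FASTb / FASTr | Retained | Diluted d | Power | Sample size multiplier (1/retained²) |
|---|---|---|---|---|
| 0% / 0% | 1.0 | 0.50 | 88.5% | 1.00 |
| 20% / 0% | 0.8 | 0.40 | 71.6% | 1.56 |
| 30% / 10% | 0.6 | 0.30 | 47.5% | 2.78 |
| 40% / 20% | 0.4 | 0.20 | 24.4% | 6.25 |

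Both models show the same pattern. If the true difference is zero, the diluted difference is zero at every level of adherence.

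**The case against.** The strongest reply is that the protocol already takes adherence seriously. The share is measured from two sources, checked every three months, and included among the moderators tested against condition. A reader might infer that the online share never enters any estimate of effect. The documents do not support that, because the Moderation subsection gives it a route into the condition model. What stands against the plan is narrower: that route conditions on a post-randomisation variable, so it gives no unbiased effect of the format, and monitoring limits drift without accounting for what remains.

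A reader might also infer that the trial is bound to find equality. That does not follow either. No adherence rate is given, adherence is described only as a possible challenge, and the disappointing implementation concerns earlier blended interventions, not FASTb. Nor do the arms differ in online share alone: eHealth tools and online aftercare belong to FASTb, although eHealth is itself counted as online time.

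Intention-to-treat answers a legitimate question, the effect of assigning FASTb as therapists deliver it. A complier-type analysis is often left to a statistical analysis plan, so its absence alone would be no fault. The point rests on what this article does fix: a companion analysis and a moderator split, neither of which meets the threat that the article itself names.

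**Conclusion.** The point holds in a limited form. Under the stated hypothesis, missed online shares bias the intention-to-treat contrast towards the expected conclusion, and the planned companion analyses do not correct for it. The size is conditional. Under the assumptions above, power for a 0.40 SD deficit falls from 89% to 60% at 70% of the intended separation and to 35% at half. Small misses matter little. The calculation rests on an assumed deficit, correlation and proportional effect, and not on any adherence figure in the protocol. It shows how far a null result could mislead, not that it will. The change is worth making before the data are analysed, because the information it needs is already being collected.

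**What to change.** - Keep intention-to-treat as the main analysis.
- In the Effectiveness and Moderation subsections, state that the split or interaction on adherence will not be used to judge effectiveness.
- Add a supportive T1-adjusted instrumental-variable analysis (two-stage least squares, of the complier-average-effect type) of the continuous outcomes. Use randomised arm as the instrument for each family's online share and include all randomised families. Take the share from the agenda registrations, which record time, as the arm definitions do; caregivers count appointments.
- Report the achieved mean separation in online share beside every effectiveness result. Limit any statement that FASTb is equally or at least as effective to the separation achieved.

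The cost is one extra analysis on data already planned, plus wording. With a single binary instrument, the analysis essentially rescales the intention-to-treat estimate. Its interval is wider and it does not restore lost power. It also assumes that arm acts only through the online share. Open allocation and therapist expectancy, which the protocol measures, may breach that assumption, so the analysis should remain supportive. A rule that the interval must exclude an important deficit would first need a stated margin. The protocol gives none, and that is a separate point.

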### Procedure

During the intake, therapists evaluate whether the clients meet the inclusion and exclusion criteria for the study. In case of doubt, therapists consult the research team in order to determine whether exclusion criteria are met. Once determined that a family can start FAST treatment, therapists ask caregivers and juveniles permission to share their contact details with the researcher. If they agree, FAST clients are approached by the main researcher or research assistants, whom all have signed a non-disclosure agreement and provided a certificate of conduct. Eligible clients receive verbal and written information about the study. The researcher obtains written informed consent from juveniles and caregivers for own participation, and from caregivers/legal representatives for juveniles younger than 16 years. After obtaining informed consent, participating families are randomized to receive FASTb or FASTr. Randomization is done on the level of the treatment site using a computerized randomization in a 1:1 ratio. Randomization outcome is shared by the researcher with both participants and participants’ therapist.

During the study, participants (juveniles and caregivers) fill out main questionnaires three times: Prior to or during the first weeks of intervention (pre-test; T1), immediately after the intervention (post-test; T2), and 6 months after termination of the intervention (6 months follow-up; T3). Therapists fill out questionnaires at T1 and T2. In addition, during the intervention, juveniles and caregivers fill out short monthly questionnaires. The number of monthly questionnaires depends on the length of intervention, which differs between five and nine months. Further, case file analysis is used to retrieve questionnaires that are filled out by juveniles, caregivers, and therapists as part of the standard FAST procedure. Official recidivism data will be collected at two-year follow-up (T4) to determine longer-term effects. For an overview of the study, see Fig. 2.

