#### Moderators

##### Demographics

Participant demographics will be obtained at T1 using a questionnaire about demographic information. The demographics questionnaire contains nine items for juveniles, 19 items for caregivers, and eight items for therapists. The items measure gender, age, and ethnicity for all respondents. Additionally, for juveniles and caregivers, family composition is measured. For caregivers, work, and financial situation are measured. For therapists, educational degrees and work experience are measured.

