#### Effectiveness

Research questions related to the effectiveness of FASTb versus FASTr on the primary and secondary outcomes will be answered using co-variance analyses with a correction for multiple testing, with the pre-test (T1) score on the dependent variable as a covariate, the post-test (T2) and 6-month follow-up (T3) scores as the dependent variable, and the condition (FASTb or FASTr) as a factor. Dichotomous outcome variables will be tested with Chi-square analysis to compare the percentage of the FASTb and FASTr conditions. Recidivism data after two years (T4) will be analyzed using Kaplan Meyer and Cox survival analyses. Effect sizes will be computed as Cohen’s d, based on adjusted means and standard errors.

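### Covariates added beyond the T1 score are chosen by significance tests of baseline differences between randomised arms, not fixed in advance on prognostic grounds

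*Protocol article*

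**What the plan says.** Under Plan of data analysis, the article compares the two arms at baseline on demographic characteristics and outcome variables. These "will be checked by means of (M)ANOVA (continuous variables) and chi-square analyses (categorical variables". The rule that follows reads: "If (some of) these variables show significant differences between FASTb and FASTr conditions, they will be entered as covariates". Its scope is stated in the same sentence: "they will be entered as covariates in all (regression) models testing the effectiveness of the intervention". No prognostic criterion goes with the rule, and no list of further covariates is given.

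Three other statements limit its reach:

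- Under Effectiveness, the covariance analyses are run "with the pre-test (T1) score on the dependent variable as a covariate". That covariate is fixed whatever the balance.
- In the same section, "Dichotomous outcome variables will be tested with Chi-square analysis", a comparison that carries no covariates.
- Recidivism at two years is analysed with Kaplan-Meier and Cox methods. Table 1 shows convictions collected at T4 only, so that model has no T1 score of its own outcome.

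On allocation, the Procedure section says "Randomization is done on the level of the treatment site using a computerized randomization in a 1:1 ratio". Because the same section has consenting families randomised, this is read here as randomisation of families within site.

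**The concern.** Randomisation makes the arms comparable in expectation. A significant test on a demographic variable therefore shows that a chance imbalance has occurred. It does not show that the variable predicts outcome. Selecting on that test can go wrong in two ways: it admits variables unrelated to outcome, and it leaves out useful predictors whenever their imbalance falls short of the threshold.

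The T1 outcome variables need a separate remark. The Procedure section allows T1 to be completed before treatment or in its opening weeks, and the allocation is disclosed to families and therapists. A T1 difference on a questionnaire may then partly reflect knowledge of the allocation or early treatment. The trigger would be worse in that case, because a variable already touched by allocation could be pulled into every regression model.

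Two things are at stake. The effectiveness model is unknown until the baseline data are in. And the precision available from prognostic variables that the trial already collects goes largely unused. Precision matters here because the hypothesis is that the two versions are equally effective, and a claim of that kind depends on a narrow confidence interval.

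**Working it through.** The article gives no figure of its own on this point, so there is none to reproduce. The checks below measure what the rule does.

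**1. How often does chance alone add a covariate?**

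Inputs: the number of candidates k is not stated. The pool is large: "The demographics questionnaire contains nine items for juveniles, 19 items for caregivers, and eight items for therapists", that is 9 + 19 + 8 = 36 items, plus the T1 outcome scores. Assumptions: each test at 0.05, tests independent, k mainly 10 to 20.

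P(at least one entry) = 1 − 0.95^k

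- k = 10: 1 − 0.95^10 = 0.40
- k = 15: 1 − 0.95^15 = 0.54
- k = 20: 1 − 0.95^20 = 0.64
- For range: k = 5 gives 0.23 and k = 36 gives 0.84.

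The expected number of chance entries is 0.05k, or 0.5 at k = 10 and 1.0 at k = 20. Positive correlation between candidates, or a multivariate test applied first, lowers these probabilities.

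**2. How large an imbalance can the rule leave uncorrected?**

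Baseline tests use all randomised participants, 100 per arm. The largest difference that stays just non-significant is about

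1.96 × √(2/100) = 0.28 SD.

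With an assumed correlation of 0.3 to 0.5 between that variable and the outcome, the shift in an unadjusted difference is

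- 0.277 × 0.3 = 0.08 SD
- 0.277 × 0.5 = 0.14 SD.

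For the continuous outcomes the T1 score absorbs part of this. As an illustration, assume a T1-outcome correlation of 0.6, a covariate-T1 correlation of 0.3 and T1 itself balanced. The partial coefficient is (r − 0.6 × 0.3)/(1 − 0.3²):

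- r = 0.3: 0.12/0.91 = 0.13, shift 0.277 × 0.13 = 0.04 SD
- r = 0.5: 0.32/0.91 = 0.35, shift 0.277 × 0.35 = 0.10 SD.

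For scale, the sample size section names d = 0.15 as the difference to be detected.

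**3. What does the rule do to power and type I error?**

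Simulation settings (all assumed): ANCOVA with the T1 score always in the model, T1-outcome coefficient 0.5, and ten independent candidates, one of them prognostic with r = 0.3 or 0.5 and uncorrelated with T1. Candidates were selected by t-test at 0.05. There were 10,000 runs under no difference and 5,000 runs at a true difference of 0.3 SD.

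| Per arm | Prognostic r | Power, T1 only | Power, significance rule | Power, covariate fixed in advance |
|---|---|---|---|---|
| 80 | 0.3 | 0.58 | 0.58 | 0.64 |
| 80 | 0.5 | 0.58 | 0.58 | 0.75 |
| 100 | 0.3 | 0.69 | 0.68 | 0.74 |
| 100 | 0.5 | 0.68 | 0.69 | 0.84 |

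Eighty per arm corresponds to the roughly 20% drop-out the article expects (100 × 0.8); 100 per arm is full retention. In these runs the rule added at least one covariate about 40% of the time, as step 1 predicts for k = 10.

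Type I error under the rule was 0.046 (r = 0.3) and 0.040 (r = 0.5) at both sample sizes. With the fixed prognostic covariate it was 0.049 to 0.053.

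**The case against.** The best defence has four parts.

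- **The main covariate is already fixed.** The T1 score is in the covariance analyses whatever the balance, and the chi-square comparisons carry no covariates. This stands. It would be wrong to say that all covariates in all effectiveness analyses are chosen by testing. It does not help the Cox model, which has no T1 score of its outcome and for which the article provides covariates only through this rule.
- **The rule is written down and looks at baseline data only.** It cannot be steered by the treatment result. This stands too, so the point is not one of analyst discretion. The content of the model still turns on chance imbalance.
- **The percentages rest on assumptions.** k is unstated, several outcome measures overlap in content, and a multivariate test is mentioned. All of this lowers the 40-64%. Likewise, the 0.08-0.14 SD shift supposes an imbalance just below the threshold and no T1 adjustment; averaged over randomisations the shift is zero.
- **The article reports no prognostic correlations.** Its Background discusses age, gender and problem severity as influences on treatment effectiveness, and recidivism risk is restricted to medium to high by the inclusion criteria. The gain in power for this trial is therefore not known. The argument for choosing covariates on prognostic grounds does not depend on which variables turn out strongest.

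A reader might also infer that a data-driven model inflates the false-positive rate. The simulation does not support that: the rule was slightly conservative.

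**Conclusion.** The point holds in limited form. Beyond the T1 score, covariates for the regression models, including the Cox model for recidivism, are selected by a criterion that carries no information on prognostic value. The consequence is a model not fixed in advance and lost precision. It is not inflated type I error, and the documents do not support the claim that every baseline difference is pure chance, since T1 questionnaires may be completed after allocation is known.

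Its size, under the stated assumptions: a 40-64% chance of at least one spurious covariate for k = 10-20; a possible uncorrected shift of up to about 0.08-0.14 SD before T1 adjustment and less after it; and essentially no power gained over T1 adjustment alone, where a covariate named in advance would add about 6 to 16 points at 80 per arm (0.58 to 0.64-0.75). The article states the rule outright, so this is not a detail left to an analysis plan. It should be changed, but it does not by itself invalidate the comparison.

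**What to change.** Delete the rule that adds covariates after a significant baseline test. Name one covariate set for the regression models, applied whatever balance is observed: the T1 score of the outcome where one exists, treatment site, and a short list of variables known before randomisation, such as age, gender and recidivism risk as rated on the RAF GGZ Youth at intake. State the set for the Cox model separately, since it has no T1 score of its outcome. Present baseline characteristics by arm descriptively, without p-values. Any further adjustment can be a named sensitivity analysis.

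The cost is a change of wording and a few degrees of freedom. All the variables are already collected, so no extra data are needed.
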